#### Mediators/moderators

We will collect data that are hypothesised to mediate loyalty scheme use, initiation (4 weeks) and maintenance of physical activity behaviour (6 months post-baseline). It is hypothesised that change in mediators should be apparent at 4–6 weeks and that mediators of early behaviour change are distinct from those affecting maintenance [52–54]. These theoretical constructs and associated outcome measures have been informed from the mapping of BCT’s from the pilot study and evidence from the relevant literature on behavioural initiation and maintenance [55–60]. Common core theoretical constructs of behaviour change including outcome expectancy [61], self-efficacy [62] and intention [63], motivation, financial motivation, planning, subjective norms, stated WTP and WTA derived from the DCEs, will be collected at baseline and 4 weeks to assess incentives to initiate behaviour change. Subjective social network data will be collected by work colleague nominations, with participants asked to nominate up to five colleagues that they usually socialise with and would also partake in physical activity with at baseline and, 6 and 18-months follow-up. Furthermore, social networks will be inferred when user’s keyfobs are “sensed” at sensors placed at physical activity opportunities in the vicinity of participating workplaces [64]. Perceptions of workplace environment [65] and objective measures of the workplace environment using Geographical Information Systems (GIS) data including walkability [66], street connectivity, access to physical activity opportunities (shops, parks, leisure facilities, train/bus stations) will be measured [67] at baseline. Other measures of web engagement, confidence in using the internet and loyalty scheme usage which may mediate intervention “dose” [68] and therefore behaviour change have been included.

To assess mediators of behaviour change maintenance, habit using the Self-Report Habit Index [69], recovery and maintenance self-efficacy [70], social norms [71], satisfaction with outcome expectancies [61], motivation, planning and social support, stated WTP and WTA, will be captured at baseline and 6 months. Data on inter-temporal and risk preferences will be collected at 6 months only (immediate post-intervention). In addition, subjective social network data will be collected at 6 and 18 months.

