### Intervention

#### Intervention group

The Physical Activity Loyalty (PAL) scheme is a complex multi-component intervention based on concepts similar to those that underpin a high-street loyalty card aimed at encouraging repeated behaviour (i.e. loyalty) [24] and is designed to incorporate a range of behaviour change techniques. Components include the provision of ‘points’ and rewards (financial incentives) contingent on meeting targeted physical activity behaviour goals (extrinsic motivation, goal-setting). Participants will be encouraged to undertake 150 mins/week of physical activity which is in line with current guidelines [33]. The PAL scheme integrates a novel physical activity tracking system with web-based monitoring and evidence-based behaviour change tools (i.e. self-monitoring, goal-setting). The proposed 6-month intervention will involve placing sensors (wifi beacons) in the vicinity of participating workplaces at specific locations to encourage physical activity within a 2 km radius of participants’ worksites (see Fig. 1) (i.e. provision of prompts/cues, habit formation, addition of objects to the environment). Locations include along footpaths, local parks, leisure centre, shopping mall, bus stops and train stations. Maps of various walking routes and details about physical activity opportunities tailored to the workplace will be provided on the study website (instruction on how to perform behaviour) [34]. Participant’s activity will be logged when they pass within an approximate 25 m radius of the wifi sensors with their PAL keyfob when undertaking physical activity (e.g. walking). This logs the place, date and time of the bout of activity. Participants can log onto their account on the study website and receive real-time feedback on minutes of their physical activity. Minutes will be converted to ‘points’ (10 ‘points’ for 1 min of activity recorded), and collected ‘points’ are redeemable for rewards (downloadable retail vouchers) sponsored by, and redeemable at, local businesses. To reduce the risk of ‘gaming’, a daily ‘points’ cap will be implemented and the transit times between sensors checked for anomalous values [27]. Bonus rewards and ‘Double Points Days’ will be offered when participants meet specific weekly physical activity targets. [17].

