#### Control group

Those assigned to the waiting-list control condition (n = 388) will be offered the opportunity to participate in the intervention after the 18-month follow-up period. Participants in this group will complete outcome measures at the same time ‘points’ as the Intervention Group.

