#### Intervention fidelity and “dose”

Fidelity of the intervention will be supported by the use of standardised training manuals and training sessions for those assisting with intervention delivery which includes the collection of the primary outcome data (pedometers) and all email communication with participants. They will be asked to keep a daily record of any problems with implementation using a customised proforma, and report to the project manager on a weekly basis throughout the 6-month intervention period. The research team will assess delivery fidelity using a quality assurance form. Weekly feedback on fidelity will be given to those involved in the delivery of the intervention to assist standardisation and completeness. Establishing intervention “dose” will draw on data regarding PAL scheme usage (minutes of physical activity/week recorded) and website exposure (e.g. frequency of visits; number of hits; number of visitors that accessed specific website content; mean duration of visits). These data will automatically be collected throughout the 6-month intervention. Extent of internet use will be assessed by asking participants how many hours per week on average they spend on the internet and to rate their confidence on using the internet on a 10-point likert scale [68]. In addition, information on those who redeemed their ‘points’ for rewards and who subsequently reimbursed their rewards at nominated retailers will be collected. Compliance with the intervention will be monitored via the PAL scheme usage data, objectively recorded using the tracking system, and the use of the web resources as outlined above.

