### Statistical analysis

For the primary analysis, mean steps per day at 6 months will be the dependent variable. A random intercept will be fitted at the cluster level (all other variables will be fixed effects), with group, organisation (in categories), and baseline mean steps per day added to the model (Objective 1). The main focus for the analysis will be the estimated coefficient representing the difference in mean steps per day between the Intervention and Control Group, adjusted for baseline differences. The model will then be extended through the inclusion of interactions involving group and relevant covariates to test for any differential effects of the intervention (e.g. age, sex, SEP, time discounting function). In light of the multiple testing involved, these subgroup analyses will be cautiously reported as hypothesis generating rather than confirmatory.

The primary analysis will then be repeated using 18-month follow-up data to investigate the effectiveness of the intervention for behaviour change maintenance (Objective 2). These analyses will be repeated with secondary health and wellbeing outcomes, and work-related outcomes (Objective 4 and 5). Further, sensitivity analyses will assess the impact of missing data using Multiple Imputation by Chained Equations (MICE), testing first whether missingness-at-random is plausible [82].

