#### Mediation analyses

Mediation analyses of early behaviour change (uptake and initiation) (4 weeks) and behaviour change maintenance (6 months from start of intervention and 12 months from cessation of intervention) will be conducted (Objective 6). Methods for assessing and estimating the direct/indirect effects of intervention in the presence of multiple mediator models will be employed [83]. Bootstrap re-sampling strategies will be used to avoid multivariate normality assumptions in placing confidence limits on the estimates of the proportion of the total intervention effect that is mediated [84]. However, these analyses must be interpreted cautiously given the limitation that the mediation model is assumed to be correctly specified both in functional form and in that no variables are omitted which affect the relationships between independent and mediator or between mediator and dependent variables.

Briefly, social networks will be constructed from the work colleague nomination data at baseline, 6 and 18 months using UCINet 6.9 [85]. These data will be supplemented by objective, real-time proximity data collected throughout the 6 month intervention period. Individual-level network variables, for example, density and centrality measures, will be derived and included in mediation analyses. Further analyses investigating the structure, characteristics, function and evolution of workplace social networks on physical activity behaviour change will be undertaken as part of a NIHR Career Development Fellowship.

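### Loyalty-scheme usage is listed as a mediator although only the intervention arm can log it, so its indirect effect on steps is biased upward and can be credited with an effect produced by other routes

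*Protocol article*

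**What the plan says.** All references are to the protocol article.

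- *Mediators/moderators* lists "Other measures of web engagement, confidence in using the internet and loyalty scheme usage which may mediate intervention" dose "and therefore behaviour change have been included".
- *Intervention fidelity and dose* defines the usage measure: "PAL scheme usage (minutes of physical activity/week recorded" by the tracking system.
- *Intervention group* explains the logging: a participant's "activity will be logged when they pass within an approximate 25 m radius of the wifi sensors with their PAL keyfob". On where the sensors stand: "Locations include along footpaths, local parks, leisure centre, shopping mall, bus stops and train stations". The keyfob is described for this group only.
- *Control group*: waiting-list participants "will be offered the opportunity to participate in the intervention after the 18-month follow-up period".
- *Mediation analyses*: "Methods for assessing and estimating the direct/indirect effects of intervention in the presence of multiple mediator models will be employed". Bootstrap limits are to be placed on the share of the total effect that is mediated. A general caution follows about model specification and omitted variables.
- *Statistical analysis*: "For the primary analysis, mean steps per day at 6 months will be the dependent variable".

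The same usage data also serve as a measure of dose and compliance and, under *Process evaluation analyses*, as a descriptive fidelity measure. Objective 6(a) treats uptake and use of the card as something to be explained by mediators, not as a mediator.

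**The concern.** An indirect effect is the product of two paths: group to mediator, and mediator to outcome given group. For scheme usage, neither path needs the scheme to have changed anyone's walking.

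The first path is positive because controls have no means of logging minutes. The second can be estimated only within the intervention arm, since usage does not vary among controls. Within that arm, someone who walks more for any reason passes more sensors and records more pedometer steps. Several sensor sites are on commuting and shopping routes, so ordinary walking is logged too.

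At stake is the mechanism claim under Objective 6. Any real benefit could be attributed to card use when it came from the emails, feedback or goal setting. If the product term is reported by itself, card use could appear to carry an effect that does not exist.

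**Working it through.** **The plan's own figures.** 1600 steps at d = 0.40 implies SD = 1600/0.40 = 4000 steps. The analysed total of 660 with 15% drop-out gives 660/0.85 = 776.5, against 776 stated. The ICC is 0.029. These set the scale; the concern does not depend on the sample size.

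**Models.** Usage = a·group + baseline steps. Steps at 6 months = c′·group + b·usage + baseline steps. Indirect effect = a·b. With the same least-squares covariates, total = c′ + a·b, so a zero total forces c′ = −a·b.

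**Assumptions not in the documents.** There are 26 clusters of 25 (650 analysed) and a baseline-to-6-month step correlation of 0.7. Usage is max(0, 40 + 30z) minutes/week in the intervention arm and 0 in controls. The within-arm correlation of z with the step residual is ρ. Inference is by cluster percentile bootstrap, stratified by arm.

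**Expected size.**
- a = 40 × 0.909 + 30 × 0.164 = 41.3 min/week.
- Usage variance = 2500 × 0.909 + 1200 × 0.164 − 41.3² ≈ 766.
- Residual SD of steps = 4000 × √(1 − 0.49 − 0.029) ≈ 2774.
- b ≈ ρ × 2774 × (30 × 0.909)/766 ≈ 98.8ρ steps per minute.
- a·b ≈ 41.3 × 98.8ρ ≈ 4080ρ, that is about 410, 820 and 1220 steps/day at ρ = 0.1, 0.2 and 0.3.

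The simulated means were 407, 779 and 1237. Divided by a true 1600-step effect owed to other routes, they are 25%, 49% and 77%.

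**Simulated error rates** (figures in parentheses are from a repeat run of 500 trials per setting):

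| ρ | No effect: a·b significant | No effect: interval for proportion mediated excludes 0 | 1600 steps by other routes: interval for proportion above 0 |
|---|---|---|---|
| 0.1 | 44% (47%) | (4%) | 39% (48%) |
| 0.2 | 94% (93%) | (5%) | 92% (93%) |
| 0.3 | 99% (100%) | (7%) | 100% (100%) |

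Across these settings the other run put the middle column at about 1–11%. Differences between runs at ρ = 0.1 are simulation error. At ρ = 0, a·b was significant in about 8% of null trials.

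**Isolating the cause.** A second set-up used 660 participants, 40 clusters, 70% keyfob uptake and no effect on steps. Here the assumed quantity is the correlation of usage with habitual walking.
- At 0.3 and 0.5 (0.11 and 0.19 with 6-month steps after baseline adjustment), the interval for a·b lay wholly above zero in 59% and 92% of trials, against a nominal 2.5%.
- At 0.5 the mean indirect effect was +594, the direct effect −602 and the total −8.
- With the same variable observed in both arms, intervals excluded zero in 4.4% and 5.2% of trials.
- With 20–60 clusters, 40–100% uptake and baseline correlations of 0.4–0.75, correlations of 0.3–0.5 gave false-positive shares of 31–100%.

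The structural zero in controls is what generates the bias.

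**The case against.** **Does the plan enter usage as a mediator?** *Mediation analyses* does not name it. Other sections treat usage as dose, compliance, fidelity or an outcome, and it is absent from the list of maintenance mediators. This stands as a limit: its mediator role rests on *Mediators/moderators* alone. That section does, however, carry the path through dose to behaviour change, and nothing later excludes usage.

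**Would the analysis come out positive whatever happened?** A reader might infer this, but the documents do not support it. The bootstrap limits are planned for the proportion mediated. Under a null total effect that ratio is unstable: in a check on the same set-up its median interval width was about 25 to 73 in proportion units. It seldom excludes zero. The high null rates apply to a·b, which may be reported because indirect effects are also to be estimated.

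**Is usage a component of the outcome?** This is also tempting and also too strong. Minutes are logged during the six-month intervention; steps come from a 7-day pedometer wear immediately afterwards and later. The problem is confounding of mediator and outcome by habitual walking, in a mediator available to one arm only. The plan's caution about omitted variables covers that type of bias in general terms, but it removes nothing from the model.

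**Are the sizes assumed?** Yes. The documents give neither ρ nor the usage distribution, and with no correlation the error is near nominal. Some positive correlation is to be expected because both variables record walking.

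**Conclusion.** The point holds in a conditional form. If usage enters the direct/indirect-effect models, its indirect effect is biased upward whenever logged minutes correlate with baseline-adjusted steps. Over assumed correlations of 0.1–0.3, a·b is falsely significant in about 44–99% of null trials. With a real 1600-step effect owed to other routes, the proportion mediated falsely credits usage with about 25–77% of it, and its interval lies above zero in 39–100% of trials. The main harm is therefore misattribution when an effect exists.

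This rests on zero usage in controls (inferred from the waiting-list design), on the assumed correlation, cluster structure and usage distribution, and on reading *Mediators/moderators* as placing usage in the mediator set. The primary comparison of steps is untouched; only secondary Objective 6 is affected. It should be changed, but it does not threaten the trial's main conclusion.

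**What to change.** In *Mediators/moderators* and *Mediation analyses*, state that loyalty-scheme usage and usage of the intervention website are excluded from the mediators in the direct/indirect-effect models. Retain only constructs measured in the same way in both arms. Report usage as dose, and label any usage–steps association within the intervention arm as descriptive.

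A complier-average estimate, with randomised group as instrument, should be at most an optional sensitivity analysis. It assumes no effect in participants below the usage threshold. *Intervention group* describes website-delivered techniques, including emails, feedback and goal setting, as effective independently of the incentive, so they could act without keyfob use. That makes the exclusion restriction doubtful, and the estimate would also be less precise than the intention-to-treat comparison.

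The cost is a change of wording with no new data. What is given up is a formal estimate of how much of the effect passes through card use, which this design cannot identify without strong assumptions.

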#### Compensatory behaviours

To assess the impact of the intervention on compensatory behaviours, data on smoking, alcohol and short Food Frequency Questionnaire (FFQ) [72] will be collected.

#### Economic evaluation

The primary economic evaluation will take the form of a within trial cost-utility and cost-effectiveness analysis, with health outcomes expressed in terms of Quality-adjusted Life Years (QALYs). Changes in health-related Quality of Life (as expressed using QALYs using EQ-5D data) will be measured from the participant’s perspective. Utilisation of healthcare resources will be captured using a specially devised online health and social care resource use data collection form. Intervention costs will be obtained using a modified template [73], explicitly discriminating between intervention and research costs.

Revealed preferences [74] and stated preferences (i.e. DCE [75]) questions will be used to gain information on the optimal level of financial incentives necessary to trigger behaviour change. Revealed preferences questions will investigate the current amount of time participants spend on activities including sleeping, leisure, work, transportation, home, physical activity and sedentary activity. The key behavioural decisions in this model are the distinct but related decisions to participate in physical activity and duration of each session of activity [76]. We will then investigate how participants’ wages, hours worked, fixed costs of physical activity (e.g. gym membership fees), and variable costs of physical activity, affect the amount of time participants spend doing physical activity [77, 78] to assess how income and substitution effects affect physical activity. Stated preferences questions and DCE questions will investigate participants’ WTA for physical activity, and the rate of trade-offs between physical activity, other time-related activities and money [79] to estimate the optimal mean level of the financial incentives that would trigger behaviour change. Information on participants’ discount rates WTA for behaviour change, and behaviour change rates will provide an understanding on how the incentive alters the costs and benefits of this healthy behaviour and why it successfully results in changed behaviour in some participants and not others.

After the intervention (at 6 months), a random sample of 200 participants will participate in a behavioural economic field experiment aimed at eliciting individuals’ inter-temporal preferences and discount rates to identify participants who exhibit exponential discounting, hyperbolic discounting or quasi-hyperbolic discounting [80]. This will help us investigate whether there is a relationship between behaviour change, discounting, and financial incentives. Briefly, the behavioural economic field experiment will be conducted in maximum groups of 20 participants during lunchtimes. Participants will be offered a £20 gift voucher for taking part in the behavioural economic field experiment. Participants will face several dichotomous decision tasks, such as a risk preference choice task and a monetary discount rate choice task. After the choice tasks, the participant will randomly select the choice occasion and the alternative that will count for payment, and will throw a 10-sided die to determine whether the final payment will take place.

#### Process evaluation

Evaluation will employ a triangulated design using both quantitative and qualitative data. The process evaluation is concerned with five core research questions: i) What was participants’ exposure to the intervention? ii) To what extent was the intervention implemented across the participating organisations? iii) How, for whom and under what circumstances does the intervention bring about behaviour change? iv) How, for whom and under what circumstances does the intervention maintain behaviour change?; (v) Whether there were any unintended consequences of the intervention. The process evaluation will encompass the following:

#### Study context

A recording of current health improvement programmes and policies in each participating organisation will be collected throughout the duration of the study period. This will be supplemented by environmental measures, (such as distance to the nearest green space and neighbourhood walkability) and free car parking at work collected at baseline, which will assess the extent of physical activity opportunities for each participating organisation.

#### Intervention fidelity and “dose”

Fidelity of the intervention will be supported by the use of standardised training manuals and training sessions for those assisting with intervention delivery which includes the collection of the primary outcome data (pedometers) and all email communication with participants. They will be asked to keep a daily record of any problems with implementation using a customised proforma, and report to the project manager on a weekly basis throughout the 6-month intervention period. The research team will assess delivery fidelity using a quality assurance form. Weekly feedback on fidelity will be given to those involved in the delivery of the intervention to assist standardisation and completeness. Establishing intervention “dose” will draw on data regarding PAL scheme usage (minutes of physical activity/week recorded) and website exposure (e.g. frequency of visits; number of hits; number of visitors that accessed specific website content; mean duration of visits). These data will automatically be collected throughout the 6-month intervention. Extent of internet use will be assessed by asking participants how many hours per week on average they spend on the internet and to rate their confidence on using the internet on a 10-point likert scale [68]. In addition, information on those who redeemed their ‘points’ for rewards and who subsequently reimbursed their rewards at nominated retailers will be collected. Compliance with the intervention will be monitored via the PAL scheme usage data, objectively recorded using the tracking system, and the use of the web resources as outlined above.

